## **Background**

Depression, one of the most common diseases in older adults, carries significant risk for morbidity and mortality . Many older adults with depression are not identified , and even when identified, over 60% of older adults fail to achieve symptomatic remission . Because of the burgeoning population of older adults, the enormous burden of late-life depression, and the limited efficacy of current antidepressants in older adults, biologically plausible models that can be translated into depression prevention efforts are needed.

Insomnia predicts depression recurrence  especially in older adults  and is a modifiable target for depression prevention. Indeed, we have found that treatment of insomnia prevents incident and recurrent major depressive disorder in non-depressed older adults . Yet, it is not known how insomnia gets converted into biological- and affective risk for depression, which is critical for identification of molecular targets for pharmacologic interventions, and for refinement of insomnia treatments that target affective responding with the potential to improve efficacy.

Sleep disturbance and/or insomnia activate inflammatory signaling and prime immune responses to subsequent inflammatory challenge . In addition, substantial evidence links inflammation to depression, as reviewed previously . Further, we and others have found that inflammation has a causative role in inducing depressive symptoms . For example, acute inflammatory challenge (i.e., endotoxin) induces depressive symptoms , which correlate with activation of brain regions implicated in depression . Finally, sleep disturbance is reported to be associated with exaggerated increases in depressive symptoms in response to endotoxin ,

with greater increases in women vs. men. Given this evidence, the present study hypothesizes that insomnia serves as a vulnerability factor for inflammation-related depression. We hypothesize that older adults with insomnia will show heightened affective responding to inflammatory challenge as compared to those without insomnia.

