## **METHODS**

### **Trial Design**

This investigation is a randomized controlled trial to evaluate the effects of an acute inflammatory challenge in response to endotoxin (0.8 ng/kg body weight) vs. placebo over 12 hours in older adults with insomnia as compared to older adults without insomnia. One hundred sixty older adults (aged 60 to 80 years), who are free from current psychiatric illness and medical conditions (e.g., inflammatory disorders), will be entered into this placebo-controlled, randomized, double-blind, parallel arm (endotoxin vs. placebo) experimental challenge protocol. Of this sample, approximately 60 participants will fulfill DSM-5 criteria for an insomnia disorder. Given the feasibility and cost utility of recruiting comparison controls who do not have insomnia, 100 controls will be used. Furthermore, a larger group of comparison controls lends more statistical power for the overall study, as well as greater statistical power for secondary analyses related, for example, to sex differences in depressive and inflammatory responses in older adults. Within each group, randomized conditions of endotoxin vs. placebo will be balanced with a 1:1 randomization ratio. Three pre-entry classification variables will be used to balance participants between those with insomnia and comparison controls including age (age 60-70 vs. 71-80), sex, and body mass index (18-24.9 vs. 25–35 kg/m^2). We will also use these pre-treatment classification variables in a modified randomization procedure, the minimization method  to ensure that the endotoxin vs. placebo conditions in the study design are balanced. The minimization method is particularly useful when it is important to balance experimental groups on a larger number of covariates . In its most simple application, this method weighs each classification variable equally and seeks to achieve an overall balance of the levels of these variables across experimental conditions, rather than a balance within each stratum. In addition, we will measure possible moderators (i.e., severity/ duration of insomnia, prior depressive episodes) and examine their potential moderating roles.

Participants will provide written informed consent as approved by the UCLA (University of California, Los Angeles) Institutional Review Board, as further described in the section on

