Ethics. All data were deidentified. Trial data monitoring and steering committees of the UCLA Clinical Translational Sciences Institute oversaw the study, which was undertaken according to the intention-to-treat principle. This study will adhere to the Consolidated Standards of Reporting Trials (CONSORT) reporting guideline.

Participants will be randomly assigned to receive either endotoxin or placebo in a 1:1 ratio in a between-subjects manner, stratified by insomnia status. Following administration of endotoxin (0.8 ng/kg body weight) vs. placebo, self- and observer rated measures of depressed mood will be assessed hourly over 12 hours (primary outcome) and self-rated measures of depressed mood and depressive symptoms every two hours over 12 hours (primary outcome). Additional secondary outcomes related to negative affective and positive affective responding will also be obtained as described below. We have found that older adults show a peak onset of depressed mood at 2 hours, similar to young adults and will explore the presence of delayed termination of response in older adults; hence protocol duration will last 12 h, as compared to 6 h as was previously used in the study of adults. Other secondary outcomes including assessment of physical symptoms, social dimensions, and inflammatory activity will be assessed as described in the detailed procedures below.

A between-subject parallel design will be used for the following reasons: 1) the proposed study involves endotoxin administration, and in a hypothetical crossover design, subjects who experience aversive sickness symptoms from endotoxin (possibly also from placebo due to expectation) might drop out, which would introduce bias and invalidate the results; 2) the effect of endotoxin on affective responding and inflammation might not resolve between two cross-over sessions of the experimental protocol; 3) repeated exposure to behavioral tests of affect responding might alter responses; 4) two cross-over sessions of the experimental protocol have higher subject burden.

Because the administration of endotoxin in this experimental protocol is designed to mimic the increases in plasma cytokines reported in chronic low-grade inflammatory conditions (i.e., 2-

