## Randomization and allocation concealment

Randomization sequence will be generated via computerized random number generator in each group for endotoxin vs. placebo in a 1:1 ratio by the study biostatistician (RO) who has no contact with participants. Allocation concealment will be maintained confidential delivery of a secure and encrypted email to the CTTC pharmacy.

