### *Statistical analysis*

Analyses will be reported according to the CONSORT statement, and will use Intent-To-Treat samples (i.e., all persons who were randomized and received either endotoxin or placebo will be included in the analysis). Measured baseline and outcome variables will be assessed for distributional qualities and transformed if necessary for use in the selected statistical models. All pre-classification variables, including age (60-70 years vs. 71-80 years), sex, and body mass

index (18-24.9 vs. 25–35 kg/m^2), as well as other baseline values will be compared between healthy controls and insomnia patients; those having a relationship with the outcome variables will be considered for inclusion as covariates in the main analyses. The detailed statistical analysis plan will be reviewed by the independent Trial Data Monitoring and Steering Committees of the UCLA Clinical Translational Sciences Institute. IBM SPSS Version 28, SAS version 9.4 or other established statistical packages will be used for all analyses.

The basic design is a 2 group (insomnia vs. comparison controls) by 2 condition (endotoxin vs. placebo), analysis variance (ANOVA) with one or more repeated measures of outcome analyzed with linear mixed models (LMM). LMM provides unbiased estimates when observations are missing at random. The timing repeated measures varies by assessment as noted above. The key results are the main effects of group, condition, and their interaction; for those analyses with repeated measures, the two main effects and interaction will further interact with the time variable.

*Primary Outcome: Depressed Mood.* The primary outcome is tested with LMM for the depressed mood subscale of the POMS and for severity of depressed mood and depressive symptoms of the MADRS with a time frame up to 12 hours.

*Secondary Outcome: Depressive Symptoms.* Change in depressive symptoms is tested with LMM for the clinician-rated assessment of depressive symptom severity as measured Hamilton Rating Scale for Depression with a time frame up to 8 hours.

*Secondary Outcome: Negative Affective Responding.* Change in negative affective responding is tested with LMM for the following behavioral tasks, Emotion Recognition Task and Emotion Intensity Task with a time frame of about 2 hours. Similar analytic strategy will be

applied for other secondary outcomes related to negative affect responding with time frames ranging from 4- to 12 hours.

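### Age, sex and BMI steer the allocation but have no assured place in the model, and the allocation method is described differently in different sections

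*Protocol*

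**What the plan says.** **Allocation.** Protocol, Trial Design, names age (60-70 vs 71-80), sex and BMI (18-24.9 vs 25-35) and states: "We will also use these pre-treatment classification variables in a modified randomization procedure, the minimization method". It explains that the method "seeks to achieve an overall balance of the levels of these variables across experimental conditions, rather than a balance within each stratum". A later paragraph of the same section says: "Participants will be randomly assigned to receive either endotoxin or placebo in a 1:1 ratio in a between-subjects manner, stratified by insomnia status". Insomnia status is the only factor named there. Protocol, Randomization and allocation concealment, says: "Randomization sequence will be generated via computerized random number generator in each group for endotoxin vs. placebo in a 1:1 ratio". That section mentions neither minimisation nor age, sex or BMI.

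**Covariates.** Protocol, Statistical analysis, takes the three classification variables, which "as well as other baseline values will be compared between healthy controls and insomnia patients", and continues: "those having a relationship with the outcome variables will be considered for inclusion as covariates in the main analyses". The same section lists the main effects of group and condition and their interaction as the key results. Under Pre-specified secondary analyses, the mediation models inherit whatever covariate set the mixed models end up with.

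**The concern.** There are three separate matters.

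- **Allocation factors in the model.** Minimisation forces the arms to be alike on age, sex and BMI. If those factors predict the outcome and the model omits them, its standard error still counts variation that the allocation has removed. The test is then conservative. The stated rule allows this outcome, because the factors enter only if they relate to the outcome, and even then are only considered.
- **The group effect.** Insomnia status is not randomised. The pool of candidate covariates is open and selection is by relation to the outcome, so the data help to decide which group contrast is estimated.
- **One allocation rule.** Whether an unadjusted test keeps its level depends on how participants were allocated, and the protocol does not describe that consistently.

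**Working it through.** The protocol gives no figure for the variance explained by age, sex and BMI, so there is none to reproduce. The share R² is an assumption, shown over a range. An effect of sex is plausible from the Background, which reports depressive responses to endotoxin in people with sleep disturbance "with greater increases in women vs. men", but no size is given.

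**Inputs from the protocol:** 60 insomnia participants and 100 controls, 1:1 within group (Trial Design); two-sided alpha 0.05 and condition effect d = .48, the low end of the cited range (Sample size). **Assumed:** three binary factors, each 50:50 with equal effects; an interaction of 1.0 SD for power.

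**Step 1, formula.** With close balance, the true variance of the condition estimate is proportional to 1 − R², while the unadjusted model uses the full variance. Hence true alpha = 2[1 − Φ(1.96/√(1 − R²))].
- R² = 0.10: √0.90 = 0.949, alpha = 0.039.
- R² = 0.20: √0.80 = 0.894, alpha = 0.028.

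**Step 2, simulation.** 4,000 trials per setting, analysed by least squares with condition, group and their interaction. Minimisation ran within each group, either deterministic or following the preferred arm with probability 0.8; each cell gives the two results in that order. The selected column keeps a factor if p < .05 with the outcome, a threshold the protocol does not set.

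| R² | Quantity | Factors omitted | Selected | All three kept |
|---|---|---|---|---|
| 0.1 | Type I, condition | .032 / .039 | .044 / .049 | .045 / .049 |
| 0.1 | Type I, interaction | .040 / .042 | .051 / .051 | .053 / .052 |
| 0.1 | Power, condition | .834 / .846 | .859 / .868 | .864 / .872 |
| 0.1 | Power, interaction | .868 / .865 | .889 / .880 | .892 / .884 |
| 0.2 | Type I, condition | .030 / .032 | .049 / .051 | .050 / .051 |
| 0.2 | Type I, interaction | .028 / .033 | .047 / .049 | .047 / .049 |
| 0.2 | Power, condition | .856 / .850 | .902 / .906 | .903 / .908 |
| 0.2 | Power, interaction | .891 / .886 | .930 / .926 | .932 / .928 |

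The power lost by omission runs from .884 − .865 = 1.9 points to .908 − .850 = 5.8 points. Selection at p < .05 stays within 1 point of full inclusion. At R² = 0 nothing is lost. At R² = 0.3 type I error with the factors omitted falls to .020-.027.

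**Step 3, the allocation matters.** Under a 1:1 permuted sequence that ignores the factors, the unadjusted condition test keeps its level (.047-.053 over R² from 0 to 0.3).

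**Step 4, tests involving time.** In a complete, balanced random-intercept model, time-constant covariates entered as main effects leave these standard errors unchanged. A check gave .2869 for condition by time and .4685 for the three-way term, each with and without the factors.

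**Step 5, the group effect.** Adjusting for a covariate changes the group estimate by its slope times the difference in its mean between groups. For randomised condition that difference is zero in expectation. For insomnia it is not when the covariate is part of insomnia or follows from it. The baseline assessments include insomnia severity, sleep quality, fatigue and depressive-symptom scales, and the inflammatory markers include baseline CRP. The protocol gives no slopes or differences, so this shift cannot be sized.

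**The case against.** **The stated rule already keeps the factors that matter.** Those related to the outcome carry the R². This largely stands. In a second simulation of 2,500 trials per setting, selection at p < .05 brought the mean standard error of the condition effect within 0.4% of full adjustment at R² of 5, 10 and 20%. A reader might take the losses in the table as the cost of the protocol's rule. They are the cost of omission, which the rule permits but does not impose.

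**Outcome-driven selection might be thought to inflate type I error.** Selection among 20 to 40 noise covariates gave .038-.052 for the randomised interaction, so no inflation is claimed for that test.

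**Comparing baseline values between insomnia and control participants is reasonable.** This stands. Group is the non-randomised factor, and Trial Design uses the same variables to balance it. The fault lies in the selection that follows.

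**Nothing says that features of insomnia will be covariates.** That is correct: Trial Design treats insomnia severity and duration and prior depression as moderators, and baseline CRP is described as possible priming. But the pool is not closed, so the exposure is a possibility and not a planned error.

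**A generated sequence need not contradict minimisation.** A reader might infer that it cannot be minimisation. That requires a list made in advance without covariates, which the protocol does not state. A random-number generator could supply the random element, and the administration section has the pharmacy receiving the assignment among the session-day steps. Nor does the text support fearing a badly uneven split of the 60 insomnia participants from an unrestricted list, since 1:1 within group is stated.

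**Covariates belong in the SAP.** A final list may well stand there. But the protocol itself states a selection rule, and that rule does not secure the factors used in allocation.

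**Conclusion.** The point holds as a correction worth making, not as a threat to the trial's validity. The factors used to allocate condition are not assured a place in the model. If they are dropped after minimisation, the between-subject condition and interaction tests run at about 0.03 to 0.04 instead of 0.05 and lose roughly 2 to 6 points of power, assuming R² of 10 to 20%, d = .48 for condition and 1.0 SD for the interaction. The error is on the conservative side. If related factors are reliably kept, the loss is negligible, and time interactions are largely untouched. The more serious exposure, which cannot be sized from the protocol, is that the group effect, a stated key result, rests on an open covariate set chosen by its relation to the outcome. Separately, the two descriptions in Trial Design and the one in Randomization and allocation concealment need reconciling. They are not shown to be incompatible.

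**What to change.** - **Statistical analysis:** include age stratum, sex and BMI stratum as fixed covariates in every primary and secondary model, whatever their relation to the outcome. Remove outcome-driven selection from the main analyses.
- **Pre-dose value:** add it as a covariate where one is collected. This cannot apply to tasks given only after dosing (Cyberball, the virtual water maze), nor where no baseline is described (PRT, EEfRT).
- **Other baseline variables:** move them to a named, labelled sensitivity analysis. The mediation models then inherit a fixed covariate set.
- **Allocation:** state one method in both paragraphs of Trial Design and in Randomization and allocation concealment. If it is minimisation, say that it runs participant by participant within the insomnia and control groups and give its random element. If it is a sequence without these factors, remove minimisation from Trial Design.

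The cost is protocol wording and three degrees of freedom. No further data or participants are needed.

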### Secondary outcomes:

*Secondary outcome: severity of depressive symptoms.* Change in severity of depressive symptoms is assessed by the observer-rater administration of the Hamilton Rating Scale for

Depression (HAMD), modified for administration during an acute time period with repeated assessment over up to 7 hours.

*Secondary outcome: negative affective responding.* Two tasks evaluate changes in negative affective responding: Emotion Recognition Task and Emotion Intensity Task, which are administered at baseline and again about 3 hours after endotoxin vs. placebo.

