## Statistical Methods

### *Sample size*

Data from several studies show that endotoxin induces increases in depressed mood as measured by the POMS with a moderate to large effects ( $d=.48$  to  $.85$ ). In addition, endotoxin induces an exaggerated increase in depressed mood in adults with modest sleep disturbance, as compared to those without sleep disturbance, with a large effect ( $d=.71$ ). Using these preliminary data, Monte Carlo simulations indicate that sample sizes ranging from 42 to 60 yield a minimum of 85% power ( $\alpha=.05$ , two-tailed) for within time comparisons of main effect of condition (i.e., endotoxin vs. placebo), main effect of group (i.e., insomnia vs. comparison controls), and the interaction of condition x group, assuming that the interaction effect in older adults is similar to effects previously reported in adults. Hence, a target sample size of  $n=60$  per condition (i.e., endotoxin, placebo) or  $n=60$  per group (i.e., insomnia, comparison control) achieves 85% power for main effect of condition, main effect of group, and their interaction. Omnibus linear mixed models LMM analysis of repeated measures of depressed mood (primary outcome) yield greater statistical power ( $>90\%$ ). In addition, oversampling of the comparison controls, per protocol, yields even greater statistical power for between comparisons of group (i.e., insomnia,  $n=60$ ; comparison control,  $n=100$ ) and condition (i.e., endotoxin,  $n=80$ ; placebo,  $n=80$ ), and within group (i.e., control).

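### Pre-dose values should always be adjusted for, not left to a covariate screen, and the primary group-by-condition test should rest on post-dose times

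*Protocol*

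**What the plan says.** Protocol, Statistical analysis, gives one model for all repeated outcomes: a two-group by two-condition "analysis variance (ANOVA) with one or more repeated measures of outcome analyzed with linear mixed models (LMM"). It continues: "The key results are the main effects of group, condition, and their interaction". The same sentence then crosses each of these effects with time wherever measures are repeated. For the secondary outcomes, it is change that this model is said to test.

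On covariates, the same section compares the classification variables and other baseline values between insomnia patients and controls. Those related to the outcomes are to be considered for inclusion. No rule says that the pre-dose value of the outcome itself is always in the model, or whether it is a level of time.

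Pre-dose values will exist. The section on endotoxin and placebo administration places baseline questionnaires and affective tasks before the bolus. Under Secondary outcomes, the two emotion tasks are those "which are administered at baseline and again about 3 hours after endotoxin vs. placebo". For mood, Trial Design reports: "We have found that older adults show a peak onset of depressed mood at 2 hours". It extends observation to 12 hours to explore whether the response ends later in older adults. Sample size bases power on comparisons within a time point and on an omnibus mixed model.

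**The concern.** The randomised comparison is endotoxin against placebo. The scientific question is whether its effect differs by insomnia status. The pre-dose rating cannot carry that effect, but it predicts the post-dose rating, so its natural use is as an adjustment.

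With no derived change score and no committed baseline term, the natural (though unstated) reading of testing change in this model is that the pre-dose rating is the first level of time. Two consequences follow:

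- The plain condition and group-by-condition terms, which are named as key results, average in a rating with no treatment effect. With one pre-dose and one post-dose measurement, that halves the effect.
- For those two-time outcomes, the effect-by-time term is exactly the change-score test, which is less precise than baseline adjustment whenever the correlation is below 1.

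The screening rule does not reliably repair this. It depends on the data, and the comparison it starts from is insomnia against control, not endotoxin against placebo. At stake is precision already paid for, on every outcome measured before dosing.

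**Working it through.** **Inputs.** From the Protocol: two-sided 0.05; about 60 participants with insomnia and 100 controls, each split 1:1, giving cells of 30/30/50/50; an effect of 0.71 for the interaction with sleep disturbance. Assumed, because the Protocol gives none: pre/post correlation ρ of 0.3, 0.5 or 0.7; equal variances (SD = 1); equal correlation between all times; normal approximation.

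**The plan's own figure.** Sample size states that 60 per condition or 60 per group "achieves 85% power for main effect of condition, main effect of group, and their interaction". Two arms of 60 give power 0.748 at d = 0.48, 0.973 at 0.71 and 0.996 at 0.85. Read as a difference of differences at one time without adjustment, the interaction has SE = √(1/30+1/30+1/50+1/50) = 0.327 and 0.71/0.327 = 2.17, so power is 0.585. With four cells of 30 it is 0.494. The stated 85% is therefore not reproduced without a correlation that the Protocol does not give; with baseline adjustment and cells of 30/30/50/50 it would need ρ of about 0.69. That is a separate sample-size matter and is not used as evidence here.

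**Two-time outcomes, such as the emotion tasks.** The variance multiplier on 0.327² is:

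- change score: 2(1−ρ)
- pre-dose value as covariate: 1−ρ²
- mean of pre-dose and post-dose (the plain two-way term): (1+ρ)/2, with the effect halved to 0.355

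| ρ | Change score: SE, power | Baseline-adjusted: SE, power | Plain two-way term: SE, power |
|---|---|---|---|
| 0.3 | 0.386, 45% | 0.312, 63% | 0.263, 27% |
| 0.5 | 0.327, 58% | 0.283, 71% | 0.283, 24% |
| 0.7 | 0.253, 80% | 0.233, 86% | 0.301, 22% |

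The variance of the adjusted estimate relative to the change score is (1−ρ²)/[2(1−ρ)] = (1+ρ)/2, that is 0.65, 0.75 or 0.85. Put the other way, the change score has 1/0.65, 1/0.75 or 1/0.85 times the variance.

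**POMS and MADRS.** Take hourly ratings from 0 to 12 h and an assumed curve (t/2)·exp(1−t/2), which peaks at 2 h. The average including the pre-dose rating keeps 40% of the peak effect; the post-dose average keeps 44% (a factor of 13/12). Interaction power at ρ = 0.3/0.5/0.7:

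- averaged, pre-dose rating included: 0.31/0.22/0.18
- averaged over post-dose times only, unadjusted: 0.36/0.25/0.20
- averaged over post-dose times, adjusted for the pre-dose value: 0.45/0.42/0.50
- the interaction-by-time test already in the plan: 0.53/0.71/0.94
- 2 h contrast, adjusted for the pre-dose value: 0.63/0.71/0.86

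For the primary outcome, removing the pre-dose rating from the average gains little by itself. Most of the gain within the averaged term comes from adjusting for it.

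Under a slower curve falling to 30% of peak at 12 h, the same five rows are 0.58/0.41/0.32, 0.64/0.47/0.37, 0.76/0.73/0.82, 0.31/0.45/0.71 and 0.63/0.71/0.86.

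**The case against.** A reader might infer that the plan averages its key effects over 12 hours and so loses a response that peaks at 2 hours. The documents do not support that: the sentence naming the key results also crosses each of them with time, and the three-way term detects a transient response. On curves that are over by about 6 hours, that planned test about matches or beats a baseline-adjusted mean of hours 1 to 4 at correlations of 0.5 to 0.7.

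A reader might also infer that the baseline covariate is discarded. It is not; it is conditional on the screen. That the pre-dose rating is a level of time is likewise an inference. The Protocol refers to a detailed analysis plan, not available for this review, which may settle it.

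It might further be argued that an early window must replace the 12-hour time frame. That does not follow. Twelve hours is the declared primary time frame, it serves a stated interest in delayed termination, and no such window appears in the Protocol. With slow decay, a baseline-adjusted 12-hour average does as well as or better than the 2-hour contrast at ρ of 0.3 and 0.5.

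Finally, a change score is unbiased for the randomised condition, so adjustment improves efficiency and corrects no bias. Insomnia status is not randomised, and adjusting its main effect for pre-dose mood changes what that effect means.

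All of this stands. What remains is that nothing in the Protocol commits to using the pre-dose value efficiently, and that the plain two-way terms named as key are weak if they include it.

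**Conclusion.** The concern holds in a limited form. The Protocol makes adjustment for the pre-dose value depend on a data-driven screen where it could simply commit to it. It also lists as key results two-way terms that are diluted if the pre-dose rating is a level of time.

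For outcomes measured once before and once after dosing, the change-score reading costs between 6 percentage points of interaction power (ρ = 0.7) and about 17 (ρ = 0.3), and the plain two-way term has only 22% to 27% power. These figures assume a 0.71 SD difference of differences, full cells of 30/30/50/50 and the stated correlations. For POMS and MADRS, the planned tests by time recover much of the loss when the response is short or moderate and less when it is prolonged, so no single power figure can be given.

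This is a change worth making because it costs almost nothing. It does not show that the planned analysis is invalid.

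**What to change.** In Statistical analysis, state that for every outcome measured before dosing:

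1. The condition and group-by-condition effects are estimated on post-dose values with the participant's own pre-dose value always in the model and exempt from the screening rule. Either enter it as a covariate interacting with time, or fit a mixed model that constrains pre-dose means to be equal between randomised conditions within each insomnia group.
2. The primary group-by-condition test uses post-dose times, not a mean that includes the pre-dose rating. Whether it is a contrast over a named window or a test across the post-dose course is for the sponsor to choose in advance. A window such as hours 1 to 4 is an option, and 12 hours may stay the primary time frame.
3. The insomnia-against-control main effect is also reported without pre-dose adjustment, because it is not randomised.

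Secondary outcomes describes the two reward tasks (PRT and EEfRT) with a post-dose timing only; if they have no pre-dose run, item 1 does not apply to them.

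The cost is wording and one extra reported estimate. No participants, visits or assessments are added.
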